### Intervention

Patients will be randomized into 2 treatment groups: arm A (control) patients will be treated with placebo before surgery in the same way and timing as the nutraceutical and arm B (experimental) patients will be treated with Micodigest 2.0 before surgery.

The Hifas da Terra company will provide Micodigest 2.0 as 30 capsules and 300 mL syrup with a syringe to measure doses. The drinkable syrup consists of organic extracts from *G lucidum*, *A blazei*, *G frondosa*, *H erinaceus*, *Pleutorus eryngii*, *P ostreatus*, *Myrciaria dubia*, and purified water, raw agave, and natural aroma. The clear vegetable capsules contain *Levilactobacillus brevis*, *Lactiplantibacillus plantarum*, magnesium stearate, silicon dioxide, and extract from *G lucidum*. This treatment is a dietary supplement that has been available since 2016; no adverse effects have been reported. The treatment dose will initiate with 10 mL/day and 1 capsule/day (before breakfast or before lunch) for 7 days and increase to 20 mL/day and 2 capsules/day (10 mL + 1 capsule before breakfast and 10 mL + 1 capsule before dinner) until surgery admission (4-6 weeks).

In the same way, the Hifas da Terra company will supply placebo as 30 capsules and 300 mL syrup with a syringe to measure doses. The drinkable syrup consists of purified water, natural aroma, and agave nectar. This syrup also includes peptin and guar gums as gelling agents and potassium sorbate as preservative. The capsules contain hydroxypropyl methylcellulose and silicon dioxide as anticaking agents and microcrystalline cellulose as a gelling agent. The treatment dose will initiate with 10 mL/day and 1 capsule/day (before breakfast or before lunch) for 7 days and increase to 20 mL/day and 2 capsules/day (10 mL + 1 capsule before breakfast and 10 mL + 1 capsule before dinner) until surgery admission (4-6 weeks).

The assigned study intervention will end if allergic reactions or any serious adverse events are reported. Additionally, patient withdrawal will be a criteria for discontinuing any intervention.

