In studies analyzing the effect of probiotics, prebiotics, and symbiotics taken prior to the admission on surgery complications, results show that the use of prebiotics reduces the risk of infections associated with surgery and length of stay without affecting other surgery complications or mortality [14]. In addition, in a meta-analysis of 34 randomized clinical trials evaluating the role of probiotics or symbiotics in surgery complications, administration reduced infectious complications during admission without effect on mortality or noninfectious complications [15].

Human intestinal microbiota is a complex ecosystem that maintains homeostasis with the intestine and plays an essential role in wound healing and immune modulation [16,17]. Consequently, microbiota alterations resulting from surgical stress and perioperative management may be associated with the presence of postoperative complications [18]. Mechanical bowel preparation and antibiotic prophylaxis for colorectal surgery have a great impact on the diversity and composition of gut microbiota. It is known that mechanical preparation can both reduce the level of nonpathogenic bacteria like *Bifidobacterium* and *Lactobacillus* and increase pathogenic bacteria like *Escherichia coli* and *Staphylococcus* [19]. Similarly, antibiotic prophylaxis and surgical stress can also impact the gut microbiota by causing changes in diversity and relative abundance [19,20]. Recent studies using animal models have shown substantial alterations in the composition of intestinal microbiota after colon resection [21]. Kong et al [22] evaluated the changes in gut microbiota using fecal samples from 43 CRC patients collected before and after surgery. After CRC surgery, the Bacteroidetes/Firmicutes ratio and the number of obligate anaerobes (including *Bacteroides*, *Bifidobacterium*, *Faecalibacterium*, *Parabacteroides*, and *Prevotella*) decreased [23]. Further, tumor-associated bacteria were eliminated, and butyrate-producing bacteria (*Bacillus*, *Bilophila*, *Barnesiella*) were reduced [23]. On the contrary, conditionally pathogenic bacteria like *Escherichia*, *Shigella*, Enterobacteriaceae, and *Streptococcus* increased [23]. Therefore, alterations of gut microbiota could promote adverse outcome in CRC patients after surgery.

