Micodigest 2.0 (Hifas da Terra) is a nutraceutical, available since 2016, that has had no adverse effects reported. Micodigest 2.0 was designed as a nutritional supplement for cancer patients. It is sold directly to the consumer for approximately 300€ (US $325.88) without a prescription from a health care professional. Micodigest 2.0 comprises 9 fungal extracts: *G lucidum*, *A blazei*, *Grifola frondosa*, *H erinaceus*, *Cordyceps sinensis*, *Inonotus obliquus*, *P ostreatus*, and *Polyporus umbellatus*. Taking into account the beneficial effects of fungal polysaccharides, we hypothesized that the fungal extract nutraceutical Micodigest 2.0 could be used to reduce complications after CRC surgery with curative intent.

For these reasons, we have designed a double-blind randomized clinical trial to evaluate the effect of Micodigest 2.0 on complications after surgery with curative intent for CRC. Apart from this purpose, we have also set the following secondary objectives:

Evaluate the safety of Micodigest 2.0 in CRC patientsEvaluate the effect of Micodigest 2.0 on fecal microbiome composition and diversityEvaluate the effect of Micodigest 2.0 on inflammatory pattern, nutrition status, and quality of lifeAnalyze the effect of the microbiome, inflammatory pattern, and nutrition status on complications after surgery

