Finally, we will perform a causal mediation analysis to measure the direct and indirect effects of Micodigest 2.0 on colorectal surgery complications. We will include as mediators the variables related to complications after surgery. This analysis will also show the total effect of other variables on colorectal surgery complications.

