## Discussion

### Principal Findings

The trial has been designed to evaluate the effects of a new dietary supplement on complications associated with surgery in CRC patients. The results, if positive, may provide a change in the current guidelines for preoperative care in CRC. Additionally, this study protocol will confirm the safety of the Micodigest 2.0 supplement and evaluate patient adherence to this new treatment. In sum, the results may provide a simple, safe, and inexpensive intervention with good adherence rates to reduce surgery complications and consequently improve the quality of life of CRC patients.

The protocol is necessary not only to study the effects of Micodigest 2.0 but also to investigate patterns and features related to complications after surgery. The results may show clinical features, inflammatory patterns, or nutritional statuses associated with postoperative complications. Moreover, the results could show new effects of gut microbiota on surgery complications. Therefore, the protocol could identify risk factors for postoperative complications and contribute to the design of new clinical studies to prevent CRC surgery complications.

Interest in the role of fungal polysaccharides in gut microbiota and immune regulation has increased in recent years. The results of this study may improve the knowledge about the biological functions of fungal polysaccharides. Further, this trial may help to define new health benefits of these bioactive polysaccharides and design new studies on their use in CRC patients. Hence, the use of fungal polysaccharides as probiotics could introduce a new step in the prevention and treatment of CRC. Bioactive polysaccharides may improve the response to treatment, especially immunotherapies, due to their immunomodulating activity. These polysaccharides could also increase the safety of treatments commonly used in cancer and alleviate adverse effects of these therapies. Additionally, the anti-inflammatory activity of fungal polysaccharides could influence carcinogenesis, progression, and tumor metastasis.

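### The active capsules contain two lactobacilli that placebo lacks, so effects belong to the whole product, not its fungal part, and ingested bacteria may be counted as microbiota change

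*Protocol article*

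**What the plan says.** All references are to the protocol article.

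- **Active capsules (Intervention).** The list that begins "The clear vegetable capsules contain" names two bacteria, Levilactobacillus brevis and Lactiplantibacillus plantarum, with a G lucidum extract and two excipients. No viability or bacterial count is given.
- **Placebo capsules (Intervention).** "The capsules contain hydroxypropyl methylcellulose and silicon dioxide as anticaking agents and microcrystalline cellulose as a gelling agent". No bacteria are listed.
- **Placebo syrup (Intervention).** "This syrup also includes peptin and guar gums as gelling agents and potassium sorbate as preservative". None of these is listed for the active syrup.
- **Hypothesis (Introduction).** It rests on the benefits of fungal polysaccharides: "we hypothesized that the fungal extract nutraceutical Micodigest 2.0 could be used to reduce complications after CRC surgery". The product description just before it lists fungal extracts only. The Objective in the Abstract likewise labels the product a fungal extract.
- **Evidence on probiotics (Introduction).** Of a meta-analysis of 34 randomized trials of probiotics or symbiotics, the article says that "administration reduced infectious complications during admission without effect on mortality or noninfectious complications".
- **Expected knowledge gain (Principal Findings).** "The results of this study may improve the knowledge about the biological functions of fungal polysaccharides".
- **Stool samples (Study Period; Fecal Samples).** They are taken at baseline and at closeout. Closeout falls at admission, when the intervention ends. The assay sequences the bacterial 16S rRNA gene.
- **Analysis (Inferential Statistics).** Microbiota diversity and composition are compared between groups with McNemar and t tests. A mediation analysis follows: "We will include as mediators the variables related to complications after surgery".

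**The concern.** The arms differ in more than fungal material, but the article's rationale and intended interpretation mention only the fungal part. Two consequences follow.

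First, attribution. By the article's own evidence, probiotics can lower infectious complications, which are part of the primary endpoint. If the active arm does better, a two-arm trial of product against placebo cannot divide the credit between fungal extracts and lactobacilli.

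Second, the microbiome result. Sequencing of a bacterial gene can register ingested bacteria as well as resident ones. The Introduction treats stimulation of Lactobacillus as a sign of fungal prebiotic activity. Capsule content recovered in stool could therefore be read as confirming the fungal mechanism, and could then be carried into the mediation analysis as a pathway.

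**Working it through.** **1. Which contrast is randomized?** Setting the two ingredient lists in Intervention side by side:

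| Component | Active | Placebo |
|---|---|---|
| Fungal extracts | yes | no |
| L. brevis and L. plantarum | yes | no |
| Syrup gelling agents and preservative | not listed | listed |

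The difference between arms estimates the joint effect of all these rows. No arm separates one row from another, so no analysis of these data identifies a fungal-only effect.

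**2. Can ingested bacteria reach the closeout sample?** Dosing continues until admission, the sample belongs to the admission visit, and no washout lies between. The assay reads bacterial DNA. An arm difference in the two administered taxa can therefore arise from ingestion alone. Nothing comparable follows for overall diversity or for other taxa.

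**3. Size.** The document has no figure for detection of these taxa, so there is nothing to reproduce on this point. The illustration below borrows the plan's 64 per arm. That number reproduces with the pooled formula at 40% v 20% and 80% power if alpha is one-sided: (1.645 × 0.648 + 0.842 × 0.632)² / 0.20² = 63.9, so 64. A two-sided 5% test would need 82. That is a separate matter and does not affect this point.

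Assume detection in 10% of placebo stools (p1) and vary the active arm (p2). With d = p2 − p1 and p̄ the mean of p1 and p2, take s0 = √[2p̄(1−p̄)/64] and s1 = √{[p1(1−p1)+p2(1−p2)]/64}. Power at two-sided .05 is Φ[(d − 1.96·s0)/s1].

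| p1 | p2 | d | s0 | s1 | Power |
|---|---|---|---|---|---|
| 10% | 15% | 0.05 | 0.0585 | 0.0583 | 13% |
| 10% | 20% | 0.10 | 0.0631 | 0.0625 | 35% |
| 10% | 30% | 0.20 | 0.0707 | 0.0685 | 82% |
| 10% | 40% | 0.30 | 0.0765 | 0.0718 | 98% |
| 10% | 60% | 0.50 | 0.0843 | 0.0718 | >99.9% |

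The answer depends almost wholly on the assumed rates. The plan also names no two-proportion test for these taxa, so the table shows only what carry-through of a given size could do.

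**4. Mediation.** Take the plan's 40% and 20% complication rates, equal arms, and an inert marker detected in 10% v 60%. Pooled over arms, the complication rate is (0.10 × 40% + 0.60 × 20%)/0.70 = 22.9% in marker-positive patients. In marker-negative patients it is (0.90 × 40% + 0.40 × 20%)/1.30 = 33.8%. If the product works by any route, a trace of the product with no causal role can look protective in a univariate screen that ignores arm. Conditioning on arm removes this association.

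**The case against.** **The trial tests a product.** The hypothesis, the intervention objectives and the mediation target are all worded for Micodigest 2.0, and a placebo without the active ingredients is what such a trial requires. This stands. A reader might infer that the hypothesis cannot be tested at all. The documents do not support that: only attribution to the fungal component is out of reach.

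**The microbiome difference is not built in.** A reader might infer that live bacteria are given and that the microbiome comparison must differ through dosing alone. No viability or count is stated, and the argument covers only the two administered taxa. This stands too.

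**The probiotic evidence is limited.** The same sentence reports no effect on noninfectious complications or mortality, while the endpoint is the overall complication rate. A reader might infer that a positive result could come entirely from the bacteria. Without dose or viability that is speculation. A contribution of their own remains plausible, and that is enough to block fungal-only attribution.

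**Mediation is partly protected.** Mediators are chosen because they relate to complications, not because they differ by arm, and outcome models in mediation analysis normally condition on arm. This weakens the concern. It leaves the univariate screening step, where the article mentions no adjustment for arm.

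**Taxon filtering is detail for a full protocol or SAP.** Its absence from an article is not in itself a fault. The fault here is that the article fixes a fungal-only reading of a product that it lists as mixed. The filtered analysis is the means of supporting any claim about resident microbiota. Filtering should not replace the main comparison, because it would remove part of the product's effect from a product-level objective.

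**Conclusion.** The point holds in limited form. The randomized comparison of complications is valid for Micodigest 2.0 as a whole and is not weakened. What the design cannot support is crediting an effect to fungal extracts or polysaccharides, as the rationale and Principal Findings lead the reader to do. The lactobacilli are one obstacle; the differing syrup ingredients are another, so setting the bacteria aside would still not isolate a fungal effect.

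For the microbiome, an arm difference in the two administered taxa may be recovered product. The stated composition comparison and mediation analysis would not distinguish it from a change in resident bacteria. The size is unknown: 13% to over 99.9% in the illustration, on assumed detection rates only. The conclusion rests on the ingredient lists being complete as printed and on the closeout sample being taken with no break in dosing.

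**What to change.** 1. Describe the product in the Abstract and Introduction as fungal extracts plus lactobacilli and other ingredients. State the hypothesis and conclusions at product level, and drop attribution to fungal polysaccharides.
2. Keep the unfiltered product-level microbiome comparison. Prespecify before unblinding a companion analysis of composition, diversity and mediation with reads of the two administered taxa removed, and report those taxa separately. Claim modulation of the resident microbiota only if the difference persists after removal.

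If a full protocol or SAP already contains the second item, only the wording remains to be changed.

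The cost is wording and a little extra analysis on sequence data already planned, with no new samples, visits or patients. The downside is that native members of the same taxa are also removed in the filtered analysis, which is one more reason to keep it beside the unfiltered result.

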### Randomization

We will randomize into the 2 parallel treatment arms using the distribution of a blinded treatment kit containing test or placebo supplementation. We will perform randomization using a code list randomly created using R software (R Foundation for Statistical Computing). This code list will include a total of 144 random numbers. Each random number will match with a unique identification code that will identify test or placebo. The randomization will ensure an equal sample size for each group. The dietary supplement will be randomly assigned into the test or placebo groups at a 1:1 ratio according to the random numbers generated.

### Blinding

This is a double-bind clinical study, so the patient and trial staff will not know the arm of allocation. The trial staff will prepare treatment kits by assigning them the identification codes following the randomization list. The kits will look exactly the same, with the name of the company, name of the drug, and information about how to take the treatment. The kit code will be identified by the principal investigator of the study only if needed for the safety of the patients.

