**Assessment**						
	Nutritional evaluation		✓		✓	
	Quality of life		✓		✓	
	Medical history		✓			✓
	Complication rate (Clavien-Dindo)					✓
	Adverse effects			✓	✓	
	Fecal and blood sample collection		✓		✓	

At visit 0, we will review inclusion and exclusion criteria. Patients who meet the criteria will be informed about the study and assigned an ID number. The principal investigator will record and keep this number appropriately. Patient will receive the informed consent and a device to collect a fecal sample at home.

At visit 1 (baseline), if patient agrees to participate in the study, we will perform randomization. We will also evaluate nutritional status and perform the quality of life assessment. Previous medical history will be recorded, fecal sample will be obtained from the patient, and blood samples will be collected. If malnutrition is detected, we will refer the patient to nutrition consultation. Additionally, the patient will receive another device to collect the needed fecal sample at the end of the study.

Follow-up visits will be performed weekly for 4 to 6 weeks. We will use this weekly phone call to collect data about adverse effects and treatment compliance.

Closeout visit will be done at the same time as patient admission. The intervention will end at this time, and patients will return the remaining treatment to researchers. We will also pick up fecal and blood samples, evaluate the nutritional status, and assess quality of life again. Further, data about adverse effects will be collected.

The end of the study will be defined by patient discharge. We will evaluate and classify the surgery complications at this time. Data collection will include information about antibiotic prophylaxis used, length of stay, vital status, surgery performed, and final staging of the CRC according to the TNM.

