#### Treatment Compliance

A staff study member will deliver treatment for 6 weeks at the baseline visit. The researchers will ask about compliance and quantity of treatment used at follow-up visits. Patient will return the remaining treatment at closeout visit. This delivery option has been proposed to minimize visits to the hospital and promote retention and completion of follow-up.

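### The Blinding section declares trial staff blind to arm, yet has trial staff code the kits from the list that reveals the arm

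*Protocol article*

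**What the plan says.** The Blinding section describes the trial as double blind, "so the patient and trial staff will not know the arm of allocation". The sentence that follows gives the coding of kits to the same group: "The trial staff will prepare treatment kits by assigning them the identification codes following the randomization list".

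The Randomization section explains what the list contains: "Each random number will match with a unique identification code that will identify test or placebo". It also says that allocation is carried out "using the distribution of a blinded treatment kit containing test or placebo supplementation".

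Two safeguards are stated under Blinding. On appearance: "The kits will look exactly the same". On code-breaking: "The kit code will be identified by the principal investigator of the study only if needed for the safety of the patients".

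Other tasks are described without a clear division of roles. In the visit descriptions below Table 1, at visit 1, "if patient agrees to participate in the study, we will perform randomization". The same subject, we, carries out the weekly telephone calls and classifies the surgical complications at discharge. Under Treatment Compliance, "A staff study member will deliver treatment for 6 weeks at the baseline visit". The Intervention section says that one company supplies both products, but does not say that they arrive already coded.

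**The concern.** One term, trial staff, covers both the people who must not know the arm and the people who work from the key. Both statements cannot be true of the same group.

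Two protections are at stake. The first is allocation concealment: a person who knows which codes are active can, knowingly or not, influence who is enrolled next. The second is blinded assessment. The primary outcome is the surgical complication rate by Clavien-Dindo grade, and the article states no minimum grade, so minor events that need judgement may count. Adverse effects and compliance are collected by telephone and are also open to influence from the person asking.

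**Working it through.** **Consistency check**

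1. Blinding, first statement: trial staff do not know the arm.
2. Blinding, next statement: trial staff put codes on kits, following the randomisation list.
3. Randomization: each code on the list corresponds to test or placebo.
4. To put the right code on the right product, the labeller must know which product is in the kit and which arm the code denotes. From 2 and 3, the labeller knows the allocation, which contradicts 1.
5. Identical appearance blinds a person who receives a finished kit. It does not blind the person who matched contents to code.
6. Restricting code-breaking to the principal investigator does not help if someone else has already worked from the list.
7. Randomisation, dispensing, weekly calls and complication grading are assigned to we, a staff study member or the researchers. Nothing separates these people from the labellers, and nothing says that they are the same individuals.

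The contradiction in 1 to 4 is stated in the text. The overlap of roles in 7 is an inference.

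**Illustration of size**

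The article gives no figure for this bias, so there is none to reproduce. Inputs from the Sample Size section are a 40% control complication rate, 64 patients per arm before the dropout allowance, and alpha .05. The two-sided test is taken here as the usual reading of the planned chi-square comparison. The share u of active-arm complications left uncounted is assumed; the document offers no source for it.

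With no true effect, both arms have a true rate of 0.40. The recorded active-arm rate is p2 = 0.40 × (1 − u).

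- u = 1/10: p2 = 0.36, apparent risk ratio 0.36/0.40 = 0.90
- u = 1/5: p2 = 0.32, apparent risk ratio 0.32/0.40 = 0.80

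Normal approximation, with d = 0.40 − p2 and p̄ = (0.40 + p2)/2:

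- SE0 = √(2 p̄(1 − p̄)/64)
- SE1 = √((0.40 × 0.60 + p2(1 − p2))/64)
- P(reject) = Φ((d − 1.96 SE0)/SE1) + Φ((−d − 1.96 SE0)/SE1)

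For u = 1/10: d = 0.04, SE0 = 0.0858, SE1 = 0.0857, giving 0.067 + 0.008 = 0.075.

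For u = 1/5: d = 0.08, SE0 = 0.0849, SE1 = 0.0846, giving 0.154 + 0.002 = 0.155 (from unrounded terms).

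Summing exact binomial probabilities over all outcomes of the uncorrected two-sided chi-square test:

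| Uncounted in active arm | Recorded rates | Normal approximation | Exact |
|---|---|---|---|
| none | 40% vs 40% | 0.050 | 0.054 |
| 1 in 10 | 40% vs 36% | 0.075 | 0.080 |
| 1 in 5 | 40% vs 32% | 0.155 | 0.162 |

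Under these assumptions the false-positive rate rises from about 5% to about 8% to 16%.

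**The case against.** The strongest reply is that the intent is clear. The kits are called blinded, they look alike, and the code is opened only for safety. Read together, this suggests that staff in contact with patients see only coded kits. The document is also a condensed article, and the name of an unblinded packer or list holder is a detail that a full protocol commonly supplies.

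Part of this stands. The absence of a named packer is not a finding, and the intent to blind is not in doubt. But the article does more than leave the packer unnamed: it gives the task to the group that it has just declared blind. The stated safeguards protect recipients of finished kits and leave out the labeller.

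A reader might infer that the same individuals label, enrol, telephone and grade, and hence that concealment and blinded assessment are both lost. The document does not support that. It uses trial staff and we without distinction, and elsewhere it names a medical doctor, a staff study member and the researchers for different tasks. If a staff member with no patient contact labels the kits, the text is followed and neither protection is lost.

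It is also fair to say that the miscount is hypothetical. At 1 in 10 the inflation is modest, which is why a range is given and not the upper figure alone.

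**Conclusion.** The point holds as a contradiction in the stated procedure. As written, some trial staff hold the allocation key while all trial staff are declared blind. Concealment and blinded grading of the primary outcome can be compromised; the text does not show that they are. How serious this is depends on whether the labellers also enrol patients or grade complications, which the article leaves open.

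The 8% to 16% range illustrates what modest differential grading would do to the type I error. It rests on the protocol's 40% rate and 64 per arm, no true effect, and an assumed 1 in 10 to 1 in 5 undercount confined to the active arm. It is not an estimate of bias in this trial. If separate unblinded packers are in fact used, the conduct is sound, but the Blinding section misdescribes it and still needs correcting.

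**What to change.** Reword the Blinding section so that the randomisation list is held, and the kits are coded, by the supplier, the hospital pharmacy or a designated person with no role in enrolment, dispensing, follow-up calls or complication grading. State that trial staff receive only pre-coded kits, and that emergency unblinding reveals one patient's code and not the list.

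Recruitment began in September 2021, so kits may already have been coded. Document who has handled the list so far and, for the remaining patients, keep those people from enrolling or grading.

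The cost is a wording change, a small change in supply logistics and possibly some reassignment of tasks among existing staff at a single centre. Treatment, sample size and analysis are unaffected.
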